#### Exploratory Prediction/Risk Profiling (Secondary, Hypothesis-Generating)

To complement explanatory regression, predictive models will be developed to explore multivariable risk profiles. Random forest models will be used to rank variable importance and detect nonlinearities/interactions, followed by parsimonious regression-based models for interpretability. Model performance will be evaluated with internal validation (eg, k-fold cross-validation), reporting discrimination (area under the curve) and classification metrics; matched pairs will be kept together within the same resampling fold to avoid leakage across training/testing splits.

#### Missing Data, Multiplicity, and Sensitivity Analyses

Missingness will be summarized by variable and time point and assessed for patterns. If missingness is nontrivial for key predictors/outcomes, multiple imputation will be considered for analyses where assumptions are plausible; complete-case analyses will be presented as sensitivity checks. For families of secondary outcomes (multiple correlated questionnaire and biomarker measures), multiplicity control will be applied using a false discovery rate approach (eg, Benjamini-Hochberg) and reported alongside unadjusted estimates to preserve interpretability. Sensitivity analyses will include assessment of incomplete matching and, where necessary, inclusion of unmatched participants with regression adjustment for matching variables. Additional sensitivity analyses will evaluate robustness to alternative model specifications (eg, excluding highly collinear predictors and alternative transformations of skewed biomarkers) and to cohort type (retrospective vs prospective).

### Ethical Considerations

The study was approved by the Clinical Research Ethics Committee of Aragón, Spain (Comité de Ética de la Investigación Clínica de Aragón; PI21/278) and will be conducted in accordance with the Declaration of Helsinki and applicable local regulations. The collection and processing of personal data will comply with the GDPR (European Union) 2016/679 and the Spanish Organic Law 3/2018 of December 5 on the protection of personal data and guarantee of digital rights.

Biological samples and associated data will be managed through the Biobank of the Aragón Health System (National Biobank Register B.0000873; PT20/00112), integrated within the Instituto de Salud Carlos III (ISCIII) Biobanks and Biomodels Platform. Samples and data will be handled according to approved standard operating procedures and under the oversight and authorization of the relevant ethics and scientific committees and will be used exclusively for the purposes described in the approved protocol.

All participants will provide written informed consent prior to any study procedures, including specific consent for biobanking where applicable. Signed consent forms will be securely archived by the principal investigator. No participant compensation is planned due to limited funding.

### Privacy and Confidentiality

Participants will be assigned a unique internal study code at enrollment. Direct identifiers will be stored separately from research data, and the reidentification key linking identifiers to study codes will be accessible only to the principal investigator and stored in a restricted, encrypted location. Analytical datasets will be deidentified (coded) and will not include direct identifiers. Data will be collected and managed using secure electronic data capture systems with role-based access controls and audit trails and stored on secure institutional servers with restricted access. Data transfers, if required, will occur only via encrypted channels. Study results will be reported in aggregate form to minimize the risk of reidentification.

## Results

### Study Status, Approvals, and Registration

ARALongCOV is a registered observational study (ISRCTN27312680) with ethics approval from the Clinical Research Ethics Committee of Aragón (PI21/278). The study is conducted under GDPR and applicable Spanish data protection legislation, with biospecimens and associated data managed through the Biobank of the Aragón Health System (PT20/00112) following approved standard operating procedures. Funding was provided by the ISCIII through project PI22/01070 (cofounded by the European Union) for the period 2023-2027.

### Timeline and Data Collection Milestones

The study combines (1) a retrospective cohort providing long-term follow-up (enabling evaluation of symptom persistence for up to 3 years) and (2) a prospective cohort enrolling newly identified Long COVID cases with follow-up assessments after baseline. Baseline assessments (T0) were initiated in late 2022/early 2023, and follow-up assessments (T1) are scheduled for late 2025/early 2026 for the earliest enrolled participants. Study assessments are conducted at 2 time points (baseline [T0] and follow-up [T1]) using the same instruments and standardized procedures to support longitudinal comparisons. Data collection is organized into 2 appointments per assessment wave, including fasting blood sampling for routine laboratory analyses and completion of online questionnaires via REDCap.

### Recruitment and Follow-up Progress

The planned recruitment target is approximately 400 participants, exceeding the minimum analyzable sample size of 155 per group derived from power considerations for detecting moderate associations in the matched case-control framework. As of February 2026, a total of 200 participants have been enrolled (n=100 Long COVID; n=100 recovered controls) and have completed T0 assessments; T1 assessments are scheduled for late 2025/early 2026.

### Planned Reporting of Findings

Primary analyses will compare matched Long COVID and recovered participants using methods that account for the paired design (eg, conditional logistic regression with pair strata) and will evaluate longitudinal change using mixed-effects models including group, time, and group × time interaction. The first manuscripts reporting baseline comparisons and longitudinal outcomes are planned for submission in the second half of 2026, followed by mechanistic/biomarker and predictive modeling outputs.

## Discussion

### Overview

In this protocol, we describe a longitudinal matched case-control study design that combines retrospective and prospective data collection to investigate the multifaceted determinants of Long COVID in adult populations; such mixed longitudinal approaches have proven useful for characterizing recovery trajectories and for linking clinical phenotypes with immune and proteomic signatures in prior cohort work [3,48,49]. Our design explicitly aims to overcome limitations of single-dimension studies by integrating clinical, functional, and laboratory domains within a single, longitudinal framework to delineate temporal relationships among symptoms, objective physiologic measures, and circulating biomarkers and thereby to identify candidate mechanistic pathways and potential intervention targets [10,14,18].

### Strengths of the Study

This is a longitudinal matched case-control (1:1 matching) design. The prospective 3-year follow-up combined with retrospective characterization permits within-participant trajectory analysis and between-group comparisons that are less susceptible to the inferential constraints of purely cross-sectional or clinic-based samples [50].

The multimodal phenotyping and biospecimen through systematic collection of validated patient-reported instruments, functional measures, and comprehensive biomarker panels enhance the potential to identify biologically coherent PASC subtypes and to relate subjective symptoms to measurable biological perturbations [10,14,49,51].

In particular, including a matched recovered control group reduces confounding by age, sex, and calendar time (including variant and vaccination epoch) and helps distinguish sequelae specifically attributable to prior SARS-CoV-2 infection from those related to general post-illness or secular effects [5,18,24].

The use of machine learning and multivariable modeling (eg, random forests for variable importance and receiver operating characteristic analyses for predictive performance) enables exploration of high-dimensional interactions [52].

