### Eligibility Criteria

Participants will be included if they have confirmed SARS-CoV-2 infection by polymerase chain reaction, antigen testing, or serology, and are aged ≥18 years. For the Long COVID group, eligibility will require persistence of symptoms for ≥12 weeks after infection onset, consistent with the World Health Organization (WHO) definition. For the control group, complete recovery will be defined as the absence of persistent or new symptoms after COVID-19. Individuals will be excluded if they refuse to participate, report preexisting symptoms similar to Long COVID prior to SARS-CoV-2 infection, or present severe psychiatric disorders or cognitive impairment that preclude informed participation.

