### Matching Strategy

Recovered controls will be individually matched 1:1 to Long COVID cases without replacement to improve baseline comparability. Matching will require exact matching on sex/gender, with flexibility of ±3 years for age and ±30 days for date of acute COVID-19 diagnosis. When multiple eligible controls are available for a given case, the selected control will be the one minimizing the absolute age difference; if ties remain, the absolute diagnosis date difference will be minimized, with random selection used only if ties persist. Each matched set will be assigned a unique pair identifier (pair_id) and retained in the analytical dataset; participants who cannot be matched within the prespecified calipers will be retained in the study database and considered in prespecified sensitivity analyses.

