**Clinical (acute COVID-19 episode)**
Date of symptom onset, symptom profile, hospitalization, intensive care unit admission, and diagnostic method (polymerase chain reaction, antigen, and serology)

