#### Primary Outcome

The primary outcome will be Long COVID status (case vs recovered control). Cases will be defined as individuals with confirmed SARS-CoV-2 infection who report persistent symptoms for ≥12 weeks after infection onset, consistent with the WHO definition. Controls will be defined as individuals with a confirmed SARS-CoV-2 infection who report complete recovery, operationalized as the absence of persistent or new symptoms after COVID-19.

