#### Biochemical and Immunological Markers

Fasting venous blood samples will be collected at baseline (T0) and follow-up (T1) to characterize participants’ biochemical, hematological, coagulation, inflammatory, and immunological profiles. All measurements will be performed in the routine hospital clinical laboratory according to standard operating procedures. Standard panels will include basic biochemistry, a complete blood count, and a coagulation profile. Systemic inflammation will be assessed using circulating inflammatory markers, including CRP and IL-6, and broader immune signatures will be characterized through cytokine profiling using a predefined panel. Humoral response to SARS-CoV-2 will be assessed using quantitative antispike immunoglobulin G serology, recorded as a continuous measure. Potential viral reactivation will be explored by measuring serological markers for latent herpesviruses, including EBV, cytomegalovirus, and HSV-1. Biomarker variables will be analyzed as candidate correlates of persistent symptoms and as longitudinal measures to evaluate change between T0 and T1.

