##### Objective 1 (Primary): Identify Factors Associated With Long COVID Status (Case vs Recovered Control)

Consistent with the study hypothesis that biopsychosocial characteristics, biomarkers, lifestyle factors, and comorbidities are associated with symptom persistence, the primary inferential analyses will model Long COVID status as the dependent variable.

As an initial descriptive step, we will summarize within-pair distributions and conduct paired comparisons as appropriate (eg, McNemar tests for binary variables; paired *t* tests, or Wilcoxon signed-rank tests for continuous variables). These comparisons will be used to describe patterns of differences and will not be used as the sole criterion for variable inclusion in multivariable models.

Adjusted associations with Long COVID status will be estimated using conditional logistic regression stratified by pair_id (matched sets), reporting adjusted odds ratios with 95% CIs. Model building will follow a prespecified, interpretable structure. A core adjustment set defined a priori will be included to address confounding not already controlled by matching (eg, acute disease severity indicators such as hospitalization/ICU admission where available, vaccination status/epoch if captured, and comorbidity burden). Candidate predictors will then be entered in clinically coherent blocks (eg, lifestyle/psychosocial block and biomarker block) to support interpretation of how associations change after adjustment for confounding and correlated predictors. Continuous predictors will be assessed for appropriate functional form (eg, linearity in the logit); flexible specifications (eg, splines) or clinically meaningful categories will be used when needed. Collinearity will be assessed (eg, variance inflation), and influential observations will be examined using standard diagnostics.

Biomarkers (routine laboratory tests, inflammatory markers including CRP and IL-6, cytokine panel, quantitative antispike immunoglobulin G, and viral reactivation serologies such as EBV/cytomegalovirus/HSV-1) will be treated as candidate correlates of Long COVID status. Continuous biomarkers will be summarized with appropriate transformations if skewed (eg, log transformation), and extreme values will be checked for plausibility and laboratory flags prior to analysis.

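### With every participant infected, the recovered controls cannot help attribute sequelae to SARS-CoV-2, and later vaccination or reinfection is not firmly covered in the antispike IgG analyses

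*Protocol article*

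**What the plan says.** Under Strengths of the Study, the article says that including a matched recovered group "reduces confounding by age, sex, and calendar time (including variant and vaccination epoch") and, in the same sentence, that it "helps distinguish sequelae specifically attributable to prior SARS-CoV-2 infection from those related to general post-illness or secular effects".

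Eligibility Criteria applies one infection requirement to everybody: "Participants will be included if they have confirmed SARS-CoV-2 infection by polymerase chain reaction, antigen testing, or serology". Primary Outcome repeats it for the comparison group: "Controls will be defined as individuals with a confirmed SARS-CoV-2 infection who report complete recovery". No other comparator is described.

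Matching Strategy reads: "Matching will require exact matching on sex/gender, with flexibility of ±3 years for age and ±30 days for date of acute COVID-19 diagnosis". The acute-episode row of Textbox 1 lists "Date of symptom onset, symptom profile, hospitalization, intensive care unit admission, and diagnostic method". Neither the Textbox nor Sociodemographic and Clinical Variables names vaccination or reinfection. Vaccination enters the analysis once, in the core adjustment set for Objective 1, as "vaccination status/epoch if captured".

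Biochemical and Immunological Markers states: "Humoral response to SARS-CoV-2 will be assessed using quantitative antispike immunoglobulin G serology, recorded as a continuous measure". That section makes biomarkers both candidate correlates of persistent symptoms and longitudinal measures of change, and Objective 1 names antispike IgG among the candidate correlates. The Objective 3 models name fixed effects for group, time and their interaction only.

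**The concern.** Two separate things are at stake.

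The first is what the study may conclude. To separate the consequences of this infection from those of illness in general, a design needs people who were not infected or who had another illness. This one has neither, yet the separation is listed as a strength and does not appear among the four limitations. A reader of the later papers could take the case-control differences as effects of SARS-CoV-2.

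The second is the interpretation of antispike IgG. Vaccination and reinfection can both raise it, and both can happen after the date on which pairs are matched. If either is distributed differently between cases and controls, an IgG difference at T0, or a difference in change to T1, can arise without any link to Long COVID. The article's own wording leaves it open whether vaccination data will exist, and reinfection is not raised. Limitations does acknowledge that vaccination patterns can influence postacute outcomes, but only as a reason why one region may not represent others.

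**Working it through.** The plan gives no figure on this point, so there is none to reproduce. The sample size calculation does not depend on it.

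**Attribution.**
- Cases (Eligibility Criteria, Primary Outcome): confirmed infection, symptoms for at least 12 weeks.
- Controls (same sections): confirmed infection, no persistent or new symptoms.
- Share with prior infection: 100% in both groups, so the difference in exposure is 100% − 100% = 0.

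A factor that does not vary between the groups cannot be credited with any difference between them. Because the groups are formed by the presence or absence of symptoms, a symptom of general post-illness origin puts a person among the cases just as a specific SARS-CoV-2 sequela would. What can be estimated is which factors accompany persistence rather than recovery, given infection.

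**What date matching does and does not cover.**
- At infection: a 30-day caliper puts both members of a pair in roughly the same variant period and the same period of vaccine availability. They also share the general background of those months, so shifts common to both groups cancel in the comparison.
- Infection to T0: not matched. The retrospective cohort was diagnosed early in the pandemic, and T0 began in late 2022/early 2023, so this interval can be long.
- T0 to T1: not matched, and about 3 years long (Lifestyle and Psychosocial Variables, Overview).
- Objective 1 model: vaccination conditional on capture; reinfection not mentioned.
- Objective 3 models: neither named. A participant random intercept absorbs stable differences between people, but not a dose or infection that falls between the two visits.

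**Possible size for antispike IgG.** Suppose recent vaccination (or reinfection) multiplies IgG by a factor k, and its frequency is p1 in cases and p0 in controls. With no true association between IgG and case status, the difference in mean log IgG is (p1 − p0) × log k, so

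geometric mean ratio = k^(p1 − p0).

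The documents give none of these inputs. The assumptions are k = 3 and a difference of 0.10 to 0.20:
- 3^0.10 = 1.12
- 3^0.20 = 1.25

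If controls have the higher uptake, the ratios invert: 1/1.12 = 0.90 and 1/1.25 = 0.80. The direction is therefore unknown as well. With equal uptake the ratio is 3^0 = 1 and there is no bias. The same formula applies to the difference in change from T0 to T1, with p1 and p0 read as uptake within that interval.

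**The case against.** The other side has real points.

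- **The wording is modest.** The article says the controls help and that matching reduces confounding. A reader might infer that it claims to isolate infection effects or to control vaccination fully; it does not. Nor does it claim that doses after infection are balanced. The calendar-time credit is fair for the moment of infection, and the mention of secular effects has some basis because shared background cancels. What has no basis is the infection-attribution part: on that, the design gives no help at all.
- **Interpretation is already restrained.** The hypothesis, the primary objective and the statistical overview speak of associations and phenotypic correlates, and no model estimates an infection effect. That limits the damage. But those cautions concern the link between candidate factors and case status; they do not correct a sentence about symptoms and infection.
- **A short variable list proves little.** Textbox 1 is a summary and is visibly incomplete: it omits the herpesvirus serologies planned elsewhere. The original protocol is an appendix not shown here. A reader might infer that vaccination and reinfection are not collected; the article does not establish that. What stands is narrower: the article itself makes adjustment for vaccination conditional on capture.
- **The magnitude is assumed.** Nothing in the documents shows that uptake differs by group. It would go too far to say that IgG differences will reflect vaccination rather than Long COVID; they could do so in part.
- **Adjustment is not neutral.** Vaccination after symptom onset may depend on being symptomatic, so requiring adjustment in every immune model, or dropping IgG altogether, would be hard to defend. This argues for confining the adjustment to IgG and showing both results.

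**Conclusion.** The point holds on both counts, in limited form. The infection-attribution clause describes a property the design lacks. This follows from the eligibility criteria alone and needs no assumption. The valid claim is about correlates of persistence versus recovery among infected adults.

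On vaccination and reinfection, date matching deals with the epoch at infection but not with individual events afterwards, and the analysis text secures neither variable. Antispike IgG is the marker most directly exposed. The size of any distortion is unknown; 1.12 to 1.25 in geometric mean ratio, or the inverse, rests wholly on the assumed 3-fold effect and 10 to 20 point difference in uptake. The sample size and the matched design are unaffected.

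**What to change.** 1. Delete the infection-attribution clause from Strengths of the Study. Limit the stated strength to differences between persistence and recovery among infected adults, with calendar-time alignment at the date of infection.
2. Replace the conditional wording on vaccination in Objective 1 with a commitment to extract vaccination dates and documented reinfections, before T0 and between T0 and T1, from health-service records where consent permits. The Aragón Health Service database is already a recruitment source.
3. Adjust the antispike IgG analyses, both at T0 and from T0 to T1, for time since last dose and for reinfection. Add a sensitivity analysis that excludes reinfected participants. Show unadjusted IgG results alongside, because vaccination after symptom onset may itself depend on case status.
4. If the data cannot be obtained, report IgG as unadjusted for vaccination and do not interpret it as a correlate of Long COVID.

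The cost is a text edit, one record extraction for the 200 people enrolled as of February 2026 (more if recruitment continues towards the target of about 400), and possibly an ethics notification. Record use for association members is described as subject to permission, so some data may remain missing. Record extraction does not depend on changing T1 forms, which may come too late for participants already assessed.

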### Limitations

Despite these strengths, several important limitations merit emphasis. First, the targeted sample size of roughly 400 participants may limit power to detect associations for low-prevalence outcomes and to perform highly stratified subgroup analyses or fully corrected high-dimensional biomarker discovery without external validation, a limitation recognized in therapeutic and mechanistic PASC research [3,23]. Second, geographic confinement to a single region (Aragón, Spain) may reduce external validity because regional differences in variant circulation, vaccination patterns, sociodemographic composition, and health care delivery can influence both exposure and postacute outcomes; this limitation underscores the rationale for multicenter and multinational replication [29]. Third, recruitment through patient associations, health-service registries, and clinical referrals risks selection bias because individuals with persistent symptoms or heightened health care engagement may be overrepresented, an issue documented across online and clinic-recruited PASC cohorts [53]. Fourth, retrospective self-report carries the potential for recall and misclassification bias, and longitudinal attrition can induce informative censoring if participants who drop out differ systematically from those retained, both of which are well-recognized challenges in longitudinal PASC investigations [4,48,50,54].

